## Abstract

**Background:**

Efforts in mental health research have long focused on the care and long-term outcomes of mental disorders. More recently, a shift in focus has occurred toward mental health promotion and prevention. One priority target population for promotion and prevention is youth with climate change–related distress. In light of the real-world threat of climate change, adaptive emotion regulation and engagement in meaningful action are 2 important strategies for promoting mental health. Ecological momentary interventions (EMIs) allow for the delivery of accessible interventions for young people with climate change–related distress, but evidence on their feasibility or beneficial effects is currently lacking.

**Objective:**

We aimed to examine the feasibility and initial signals of efficacy of the Climate Mind and Act (CliMACT) training, a novel hybrid EMI for mental health promotion in youth with climate change–related distress.

**Methods:**

A 2-arm, parallel-group, and assessor- and analyst-blinded feasibility randomized controlled trial (RCT) will be conducted in 50 young people aged 14-25 years with climate change–related distress, who will be allocated on a 1:1 ratio to the experimental condition (CliMACT training + care as usual [CAU]) or the control condition (CAU only). CliMACT involves 3 sessions with a mental health professional and 6-week access to a smartphone-based EMI to support the real-world transfer of training content based on compassion-focused interventions and acceptance and commitment therapy. The EMI delivery schemes involve enhancing (introducing new EMI components), consolidating (training of EMI components), and adaptive (triggered in moments of higher negative affect) components. CAU involves access to all standard health care and social services. Feasibility criteria of the trial methodology include recruitment, randomization, and retention. Feasibility outcomes of delivering the CliMACT training include participant satisfaction, participant adherence, and mental health professionals’ fidelity to the training protocol. Initial signals of efficacy on mental health candidate outcomes and mechanisms will be explored. As feasibility criteria for a priori planned subgroup analyses, credibility criteria will be established and distributions of indicators for health inequities explored. Feasibility criteria for measuring costs of care and service use and health-related quality of life for an economic evaluation in a future definitive RCT will include exploring response distributions across groups. Candidate outcomes and mechanisms will be assessed at baseline, post training, and 4-week follow-up, using self-report and 6 days of ecological momentary assessment.

**Results:**

The first enrollment took place in December 2024. Data collection was completed by August 25, 2025. Results are expected for publication in 2026.

**Conclusions:**

To our knowledge, this is the first study to establish the feasibility and initial signals of efficacy of an EMI, targeted specifically at young people with climate change–related distress. If feasibility can be established, the trial will inform a future fully powered efficacy-effectiveness RCT, accompanied by an economic evaluation.

**Trial Registration:**

ISRCTN ISRCTN33613914; https://doi.org/10.1186/ISRCTN33613914

**International Registered Report Identifier (IRRID):**

DERR1-10.2196/77764

## Introduction

### Background

Climate change is one of the current societal challenges recognized to pose a threat to mental health. While it is commonly agreed that negative emotional reactions toward the real threat of climate change are natural and common [1], in a substantial proportion of individuals, climate change–related distress is related to impairment in daily life, including difficulties with sleeping, concentrating, or fulfilling daily roles [2-5]. For example, in a large survey among young people in Germany, 65% reported negative emotions in relation to climate change, and about 20% reported experiencing sleep problems and a limited sense of joy due to their concerns about climate change [2]. These findings indicate that youth with climate change–related distress may be one priority target population, but scalable strategies for mental health promotion and prevention remain very limited.

The recent rapid advances in digital technologies offer new avenues for ecological translation (ie, daily life application) of accessible and scalable mental health promotion [6,7], including for young people with climate change–related distress. Ecological momentary interventions (EMI) provide a unique opportunity for real-life and real-world transfer of therapeutic, preventive, or promotional principles, tailored to the person, moment, and context [8-12]. Due to their accessible and personalized nature, EMIs are a promising intervention method for ecological translation to the living environments of vulnerable groups. Thus, EMIs are a potential scalable digital intervention option for young people with climate change–related distress. While overall, there is evidence on acceptability, safety, and efficacy of EMIs for the prevention and early intervention in young people with early mental health problems [13-16], this remains to be established among young people with climate change–related distress in a target group-specific and vulnerability-sensitive approach.

While there is a lack of evidence with interventions among the target group, conceptual work on fostering resilience in young people with climate change–related distress indicates that interventions focused on the individual should consist of 2 strands: one enabling adaptation, which includes the successful regulation of stressful emotions, and one focusing on action, enabling youth to engage in meaningful transformation of their environments and living conditions [17-19]. In a recent feasibility randomized controlled trial (RCT), we found strong evidence for the safety and feasibility of trial methodology and intervention delivery for EMIcompass, a novel, transdiagnostic EMI intervention based on principles of compassion-focused interventions (CFI) for enhancing emotional resilience in youth with early mental health problems [16]. The feasibility RCT also revealed initial signals of efficacy for reduced momentary stress reactivity, and improved quality of life and momentary emotional resilience. These findings support using and adapting training components from EMIcompass for targeting emotion regulation in the target population of young people with climate change–related distress. Evidence has further shown that focusing on action and, more specifically, on meaning-focused coping in relation to climate change is related to more positive mental health outcomes [20]. This could support incorporating principles of acceptance and commitment therapy (ACT) into a training geared toward promoting mental health in youth with climate change–related distress. This includes encouraging distressed youth to choose and engage in actions that are aligned with their own values, as proposed by Niessen and Peter [18], and is further supported by ecological momentary assessment (EMA) research showing that value-based action is associated with better well-being [21]. Interventions based on ACT have shown promising results as a transdiagnostic approach for reducing stress in young people [22]. There is further evidence to suggest that digital interventions based on ACT principles for young people have stronger effects in targeted as compared to universal strategies for intervention [23]. Therefore, the current study adopts a targeted approach to bolster the mental health of young people who experience climate change–related distress. Taken together, CFI and ACT offer promising intervention principles and techniques amenable to being implemented in an EMI for reducing climate change–related distress in young people, but evidence on the feasibility of its delivery in this target population is lacking.

As underlying candidate mechanisms of change, transdiagnostic third-wave behavioral interventions such as CFI and ACT use techniques expected to foster mental health by enhancing self-compassion, mindfulness, psychological flexibility, and emotion regulation [24-26]. As a further candidate mechanism, in this particular target group and proposed intervention, value-based action may manifest in proenvironmental behavior (PEB) [27]. Acquiring both CFI- or ACT-based skills and strategies may moreover promote rather nonspecific candidate mechanisms such as emotional resilience and self-efficacy. As candidate outcomes, reduction of psychological distress or symptoms is often considered a secondary rather than primary aim of third-wave behavioral interventions [24,28]. In line with extensive literature that mental health is much more than the absence of psychopathology [29], candidate outcomes of a mental health promotion or prevention training for young people with climate change–related distress ought to include indicators of positive mental health, such as mental well-being, quality of life (including the emotional and social domain), and happiness. In a second vein, candidate outcomes include climate change distress and impairment itself, as well as general psychological distress often associated with the former [30].

Building on a marginalized population approach, population-based strategies for improving mental health may inadvertently augment the long-documented inequities in health among marginalized groups, who, for example, due to social position, limited resources, or problems with access, may benefit less from such strategies [31,32]. Developing novel intervention and training approaches, therefore, requires us to monitor and mitigate the potential of exacerbation of inequities, which may be caused by differential reach of and effectiveness for groups in marginalized or vulnerable positions. Urbanicity, low socioeconomic status (SES), lower education, female gender, and migrant and ethnic minority group status reflect indicators of socioenvironmental and ethnic mental health inequities also highlighted in the PROGRESS (Place of Residence; Race, Ethnicity, Culture, or Language; Occupation; Gender or Sex; Religion; Education; Socioeconomic Status; and Social Capital)–plus framework for equity in health [33,34]. Crucially, they have also been reported to play a direct or indirect role in accelerating the impact of climate change on mental health [5,35-37]. Despite evidence on initial signals of efficacy for the EMIcompass intervention [16], evidence in young people with climate change–related distress on target group- and training-specific candidate outcomes and mechanisms, taking relevant indicators of inequities in health into account, is pending.

### This Study

This study aims to investigate the feasibility and initial signals of efficacy of the CliMACT (Climate Mind and Act) training, a novel hybrid EMI for mental health promotion in youth with climate change–related distress, in addition to access to all standard health care and social services (care as usual [CAU]), compared with CAU only in a feasibility RCT (ISRCTN33613914). Feasibility criteria are based on the principles of the CONSORT (Consolidated Standards of Reporting Trials) extension for pilot and feasibility trials [38] and adapted from the study by Reininghaus et al [16]. To achieve the overall aim, we will first, examine the feasibility of the trial methodology (based on recruitment, randomization, and retention). Second, we will examine the feasibility of delivering the CliMACT training (based on participant satisfaction, participant adherence, and fidelity to the training protocol) and explore its specific and nonspecific active ingredients (CliMACT training components; working alliance toward mental health professionals and toward the EMI). Third, we will explore signals of efficacy of the CliMACT training on candidate outcomes, that is, positive mental health (quality of life [psychological and social domain], happiness, and mental well-being), climate change distress and psychological distress, as well as on momentary affect and momentary climate change–related distress at posttraining and 4-week follow-up. Fourth, we explore signals of efficacy of the CliMACT training on candidate mechanisms of change, namely self-compassion, mindfulness, psychological inflexibility, self-efficacy, resilience, PEB, emotion regulation, internalized stigma, and experience of discrimination, self-stigma of help-seeking, as well as on momentary emotional resilience, momentary self-efficacy, momentary PEB, and momentary value-based living at posttraining and 4-week follow-up. Fifth, we examine the feasibility of establishing credibility criteria for an a priori planned subgroup analyses on social and ethnic inequities in health by exploring the distribution of indicators for health inequities relevant to climate change–related distress, and exploring the effects of the CliMACT training stratified by marginalized or vulnerable group status (defined as meeting any of the following criteria: gender not male, ethnic minority, migration history, low family SES, current urbanicity, or lower education level). Sixth, we examine the feasibility of measuring related costs of care and service use and health-related quality of life for the accompanying economic evaluation in a future definitive RCT, and explore the distribution of cost patterns across the experimental and control groups.

## Methods

### Cocreation

At the outset of this study, a society advisory group (SAG) including representatives from national mental health–related umbrella organizations, lived experience experts, policy makers, and mental health practitioners was set up in Mannheim, Germany. The SAG leads the research cocreation process in collaboration with the research team throughout the project. Throughout the project, the SAG will meet with the research team and be involved in decisions about this study’s design, interpretation of findings, knowledge integration, dissemination, and development of a scaling strategy. Consultation meetings will be held at least annually and at key decision points (eg, after completing analyses on feasibility and initial efficacy signals). Representatives from the group with lived experience will receive financial compensation for contributing their personal time. Before the start of the feasibility RCT, a set of potential scenarios for intervention was cocreated with SAG members based on desk reviews and consultation meetings. The intervention scenarios specified different target groups, recruitment sites, and strategies, and the training delivery mode. The selection of a final intervention scenario was carried out by SAGs and other stakeholders in the mental health field using a set of methods (ie, a Delphi panel and scenario-based workshops) that are described in detail elsewhere [39]. The scenario selected will target a broader group of young people with climate change–related distress, with recruitment strategies focusing on Mannheim and the Rhine-Neckar region, including sites as outlined in the Recruitment section. Stakeholders favored a hybrid intervention, including access to a smartphone-based EMI combined with facilitating face-to-face sessions with a mental health professional.

### Study Design

This feasibility study protocol follows the CONSORT 2010 statement extension to randomized pilot and feasibility trials (Multimedia Appendix 1). In a 2-arm, parallel-group, assessor- and analyst-blinded feasibility RCT, 50 individuals aged 14-25 years with climate change–related distress will be randomly allocated to (1) the CliMACT training in addition to CAU or (2) CAU only at a 1:1 ratio. Potentially eligible participants will be prescreened for eligibility in a phone call. Participants will then complete informed consent procedures with an authorized member of this study’s team, followed by the completion of questionnaires to establish eligibility. Next, outcome data will be collected at baseline (*t*_0_), at the end of the 6-week training period (*t*_1_), and at a 4-week follow-up (*t*_2_; Figure 1). Randomization takes place after baseline assessment. Hence, the full duration of this study’s period for participants will be approximately 3.5 months (depending on the time between informed consent and completion of baseline assessment). Participants can withdraw consent from participation at any time. Participation will be terminated prematurely if participants are at risk for harm to themselves or others.

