#### Exclusion Criteria

Young people are excluded from participation if they (1) report current treatment for or a current diagnosis of a severe mental disorder which they received from a professional (*ICD-10* [*International Statistical Classification of Diseases, Tenth Revision*] codes: F32.2, F32.3, F20, F22-29, F30.x, F60.3) or (2) report a significant reduction in functioning in the past 30 days (World Health Organization Disability Assessment Schedule 2.0 ≥41) [41]. The World Health Organization Disability Assessment Schedule 2.0 cutoff for exclusion is based on population norms, representing the 90th percentile on the 36-item version [41]. Other exclusion criteria comprise (3) indications of acute risk to self or others, (4) the inability to provide informed consent, and, in case of minors, no consent by parents or legal guardians, and (5) insufficient German language abilities, per assessment of the investigator.

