#### Experimental Condition: CliMACT+CAU

##### Overview

Participants allocated to the experimental condition receive the CliMACT training in addition to CAU. CliMACT will be delivered over a 6-week training period. It consists of an app-based, adaptive EMI and 3 sessions with a trained mental health professional, with a duration of 45-60 minutes, administered on-site or online using a certified and encrypted videoconferencing system. The EMI is geared toward real-time and real-world transfer of training content, principles, and techniques from face-to-face sessions to individuals’ daily lives using an app- and web-based system (InteractionDesigner platform, movisens GmbH). The CliMACT training is based on principles of CFI as well as ACT. Multimedia Appendix 2 provides an overview of the key training components during the 6-week training period. The EMI consists of 3 different delivery schemes of EMI components and EMA-based monitoring.

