##### EMA-Based Monitoring and Feedback

CliMACT allows young people and mental health professionals to monitor young people’s well-being by delivering visual feedback in terms of reported climate change–related events, activities, affect, and completed training components, via the app and a web-based dashboard function.

The app further uses gamification elements to encourage practice and visualize progress throughout the 6 weeks. It provides FAQs (frequently asked questions) on training-relevant matters and web links to local and national climate change and sustainability-related topics and organizations to demonstrate network opportunities for collective action. The finalized CliMACT training manual, developed as part of the ADVANCE (Addressing Mental Health Vulnerabilities From Adolescence to Older Age: Innovating Prevention Science for Times of Change) project, will be published.

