Using EMA (movisensXS app, movisens GmbH), 18 items are used to assess momentary affect on a Visual Analog Scale (VAS) ranging from 0-100. In this study, the mean of 4 unipolar positive affect facet items will be used as the total positive affect score. The mean of 9 unipolar negative affect items will be used as the total negative affect score. Based on the CC-DIS [3], 6 items are used to measure momentary climate change distress (3 items) and impairment (3 items), using a 7-point Likert scale ranging from 1-7. Mean scores will be used as scale scores. During the training phase, participants in the experimental condition complete an abbreviated EMA form in the InteractionDesigner platform, including 11 items assessing momentary affect on a 7-point Likert scale and a multi-select item to indicate which specific affects are currently related to climate change. All EMA items can be found in Multimedia Appendix 3.

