#### Other Measures

At each assessment, it will be documented if any adverse events (AEs) related or unrelated to the training or study participation have occurred, including health-related events, technical problems with the smartphone, problems with the digital application, or other issues. Marginalized or vulnerable group status is reflected by equity-relevant sociodemographic indicators at baseline and coded present when at least one of the following is true: female gender, ethnic minority, migration history, low family SES, current urbanicity, and lower education level. At posttraining, adverse trial effects are measured with the measure by Hutton et al [82], using a 5-point Likert scale ranging from 1-5. An overview of all measures and time points can be found in Figure 2 (in line with the SPIRIT [Standard Protocol Items: Recommendations for Interventional Trials] statement [83]).

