#### Initial Signals of Efficacy on Candidate Outcomes and Mechanisms

Initial signals of efficacy of the CliMACT training will be explored according to the intention-to-treat principle (ie, data of all participants randomized to 1 of the 2 conditions will be entered into the analysis). Before data analysis, all data will be checked for quality and plausibility. For all analyses, we will inspect the 95% CI and obtain d-type effect sizes given their exploratory nature. Linear mixed modeling will be used to compare candidate outcomes (objective 3) and candidate mechanisms (objective 4) between the experimental and control conditions at posttraining and 4-week follow-up. Each candidate outcome and mechanism (applying joint analyses to posttraining and 4-week follow-up assessment) will be used as a dependent variable in separate analyses. Time (posttraining and 4-week follow-up), condition (experimental and control condition), and the respective outcome measured at baseline (grand-mean centered) will be entered as independent variables. A level-2 random intercept will be added, and level-1 residuals will be allowed to be correlated to account for within-subject nesting of repeated measures. Restricted maximum likelihood estimation will be applied. The coefficient for the condition reflects the difference between the intervention and control arm for the post- and 4-week follow-up assessments jointly. We will next extend the model by a condition × time interaction to determine the time-specific contrasts, reflecting differences between the 2 conditions at each time point, and an outcome or mechanism at baseline × time interaction.

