## Discussion

As the main objective, this study will provide evidence on the feasibility of trial methodology (based on recruitment, randomization, and retention) as well as the feasibility of delivering the CliMACT training (based on satisfaction, compliance, and fidelity with the training manual). In addition, it will provide the first evidence on initial signals of efficacy of the CliMACT training on candidate outcomes and mechanisms. Climate change–related distress is common in youth [2,4]. To date, strategies for mental health promotion and prevention in this population are limited. Especially, evidence-based strategies to support this population using EMIs tailored to person, moment, and context are currently lacking. Therefore, the primary aim of this study will be to evaluate the feasibility of a hybrid adaptive EMI for mental health promotion in young people with climate change–related distress. The approach that we adopt here focuses on the ecological translation of CFI-based and ACT-based principles to the daily lives of young people with climate change–related distress.

Based on findings on feasibility of trial methodology from the current feasibility RCT, we will decide on necessary adaptations about recruitment sites and strategies (eg, moving from local to nationwide recruitment), the randomization procedure (eg, exposing errors), and strategies to maintain or improve retention (eg, optimize documentation, notification of participants, incentives, and reduction of number of measures). Based on findings on the feasibility of delivering the CliMACT training, we will improve intervention delivery based on quantitative and qualitative data on face-to-face sessions and EMI (eg, training components, frequency of EMAs, and visualizations), and optimize acceptability of the training in a future efficacy-effectiveness RCT. Initial signals of efficacy from the feasibility RCT will, based on effect size estimates, support the selection of a primary outcome for an efficacy-effectiveness RCT and will help us to formulate a more accurate theory of change model, which will be tested in the future.

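### As worded, the risk-of-harm rule ends trial participation, not only the training, and the article provides for no outcome assessment afterwards

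*Protocol article*

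**What the plan says.** The rule stands in the protocol article under Study Design: "Participation will be terminated prematurely if participants are at risk for harm to themselves or others". The sentence before it uses the same noun for consent to the study. Exclusion Criteria uses it for entry to the trial: "Young people are excluded from participation if they". Other Measures names the training and study participation as two separate things.

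The efficacy analysis (Initial Signals of Efficacy on Candidate Outcomes and Mechanisms) follows intention to treat. Its dependent variable is the post-baseline score, "applying joint analyses to posttraining and 4-week follow-up assessment", and the baseline score enters only as a covariate. Other Measures fixes one harm-related questionnaire at a single visit: "At posttraining, adverse trial effects are measured".

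Only the experimental arm receives "3 sessions with a trained mental health professional" (Experimental Condition, Overview). In the training phase "participants in the experimental condition complete an abbreviated EMA form" (Candidate Outcomes), and "CliMACT allows young people and mental health professionals to monitor" well-being through a dashboard (EMA-Based Monitoring and Feedback).

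The Discussion says that the effect sizes will "support the selection of a primary outcome for an efficacy-effectiveness RCT".

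**The concern.** A rule that ends the trial for a participant does more than a rule that ends the treatment. The safety purpose is met by stopping the training, lifting the EMA burden and referring the person. Ending outcome assessment as well removes the t1 and t2 scores of people selected because they got worse, and the trigger lies close to the distress and well-being outcomes under study. The same people would not fill in the posttraining measure of adverse trial effects, although their answers matter most there.

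The loss could also be uneven. Three conversations with a trained professional give more occasions to notice risk in the experimental arm than in the control arm. If a few worsened participants are missing mainly from the trained arm, its distress and well-being results look somewhat better than they are. Those estimates feed the choice of primary outcome for the next trial, and the rule itself may be carried into that trial.

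**Working it through.** **1. What participation refers to.** Four places point to the trial as a whole: the preceding sentence in Study Design (withdrawal of consent to the study), Exclusion Criteria (entry to the trial), Other Measures (training and study participation listed separately), and the scope of the rule. It applies to all participants, and the control arm has no training to stop.

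**2. Whether assessment continues after a stop.** No section says so. Randomization and Blinding does state, for the case of unblinding, that another team member carries on with follow-up assessment. No matching provision is made for a risk termination.

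**3. What the model does with such a participant.** The response is the t1 and t2 score.
- Stopped before t1: no response row. Only the baseline value is known, and the model cannot use it without a post-baseline score.
- Stopped between t1 and t2: the observed t1 score enters the joint model, so the loss is smaller.

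A likelihood-based mixed model relies on data being missing at random given what was observed. Before t1, only baseline could carry information about a later deterioration.

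**4. Size, as an illustration only.** The article gives no expected number of risk terminations and no figure that could be reproduced here.

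Input from the document: 25 per arm (Justification of Sample Size).

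Assumed inputs: k = 1 or 2 stopped before t1, in one arm only; D = 1 or 2 SD worse than those retained, after baseline adjustment.

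If the retained mean is m, the full-arm mean is [(25 − k)m + k(m − D)]/25 = m − kD/25. The retained mean is therefore too favourable by kD/25:

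| k | D (SD) | shift (SD) |
|---|---|---|
| 1 | 1 | 1/25 = 0.04 |
| 1 | 2 | 2/25 = 0.08 |
| 2 | 1 | 2/25 = 0.08 |
| 2 | 2 | 4/25 = 0.16 |

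For comparison, the half-width of an unadjusted 95% CI for the arm difference at one time point is 1.96 × √(2/25) = 0.554 SD. The shift is 0.04/0.554 = 7% to 0.16/0.554 = 29% of that half-width.

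If both arms lose the same number with the same deficit, the shifts cancel and the contrast is unaffected. With k = 0 there is no effect.

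**The case against.** The strongest reply is that the loss of t1/t2 data is inferred. The rule is one summary sentence in a journal article. What follows a termination (referral, safety contact, which assessments are still offered) may be set out in the full protocol, which is not shown. This stands as a limit on confidence. It does not remove the point, because the published sentence is a stated rule and, as worded, it ends trial participation.

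Second, this is partly a clinical judgement in a sample that includes minors, under procedures approved by the ethics committee. That also stands, and the clinical decision to stop is not questioned here.

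Third, the shift rests on assumed inputs. Acute risk, severe mental disorder and marked loss of functioning are excluded at entry, so zero cases is plausible. The efficacy analyses are exploratory, and the Discussion already warns of uncertain effect sizes. Missing the same worsened people would tend to move distress and well-being estimates in the same direction, and nothing shows that the ranking of candidate outcomes would change.

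A reader might infer more than the documents support:
- *That intention to treat is contradicted.* It is not. The principle as worded concerns who enters the analysis, and a missing outcome does not break it.
- *That harms go unrecorded.* Safety Considerations commits to collecting adverse and serious adverse events throughout the study period. The gap is the one posttraining questionnaire.
- *That the EMA and dashboard make detection of risk clearly unequal.* The training-phase items cover affect, activities and events. No risk item is described, nor any screening of the dashboard for risk. The case for unequal detection rests mainly on the three sessions.
- *That retention is miscounted.* Counting these stops as losses is correct.

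**Conclusion.** The point holds as a minor one, with low confidence about its practical effect. As worded, the rule ends the trial for a participant at risk of harm, and the article makes no provision for later outcome assessment. A stop before t1 would then leave missing outcomes that are related to the distress and well-being measures and possibly uneven between arms. The illustrative shift of 0.04 to 0.16 SD in one arm's mean depends wholly on the assumed 1 or 2 cases in one arm and the assumed 1 to 2 SD deficit. It is well inside the half-width of about 0.55 SD. The document does not establish that any such case occurred, that follow-up was in fact refused, or that the efficacy estimates are biased.

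**What to change.** Reword the sentence in Study Design so that risk of harm ends the training and the EMA and leads to referral. The t1 and t2 questionnaires, including the adverse-trial-effects measure, are still offered where this is clinically safe and the participant (and guardian, for minors) agrees. The clinical decision to stop stays as it is. If the full protocol already allows this, the article's sentence only needs to say so.

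Data collection has finished, so the rule cannot change in this trial. In the results, report risk terminations by arm, by timing (before or after t1) and by reason, and read the exploratory effect sizes alongside those counts. Change the rule before it is carried into the definitive RCT.

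The cost is one sentence in the protocol and one line by arm in the report, using existing visits and staff. The downside is limited further contact with a few at-risk participants, some of them minors. The gain is partial, since some people at acute risk would not complete the questionnaires even if asked.
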